#### **Interventions**

##### **Control group**

During term 1 2009 (March and April 2009), control schools will have an in-class session, led by the school liaison research assistant, to discuss hand hygiene. The content was developed in collaboration with Public Health Nurses in Dunedin, who have in previous years had a rolling programme of hand hygiene education in schools. The session covers the reasons why and when hand hygiene is important and hand washing technique, including a demonstration of the importance of thorough washing using an ultra-violet light-sensitive cream, Glo Germ™. The same session will be used for the intervention group, with the addition of a discussion about the hand sanitiser. The purpose of this session is to ensure that the two groups are equivalent with respect to hand hygiene knowledge (or at least having had the opportunity to acquire hand hygiene knowledge) at the beginning of the study. The content of the hand hygiene education sessions is available in Additional files 1, 2, 3 (Hand hygiene education session: years 1 and 2; Hand hygiene education session: years 3 and 4; Hand hygiene education session: years 5 and 6).

##### **Intervention group**

Intervention schools will have the in-class session described above to discuss hand hygiene and to be instructed in the use of the hand sanitiser during term 1, 2009 (March and April 2009). No-touch dispensers will be fitted in all classrooms during the first school holidays in 2009 (April 2009). The hand sanitiser will be at least 60% alcohol.

Children will be able to use the sanitiser at any time they wish, but teachers will be asked to ensure that the children use the hand sanitiser after coughing/sneezing/blowing their nose, and as they leave for morning break and for the lunch break. These times have been chosen for two reasons. First, this will allow the slightly unpleasant smell of the sanitiser (following use by the whole class) to disperse before the children return to the classrooms. Second, break times are when transmission is likely to be higher from children touching one another.

The hand sanitisers will be placed in classrooms to ensure that there will be some teacher oversight of their use, minimising the chances of children playing with the dispensers and sanitiser, and of children getting squirted in the eyes or mouth.

#### **Timing of recruitment, intervention, and follow-up**

School principals will be contacted for potential inclusion in the trial in November 2008. Parents of randomly selected children will be mailed an information sheet and consent form during term 1, March 2009, to seek consent to participate in post-absence interviews.

All schools will be given a single health education session on hand hygiene during term 1, (March and April) 2009. Hand sanitisers will be present in the intervention schools during terms 2 and 3, 27 April to 25 September 2009.

Absence information will be collected for a total of twenty school weeks from the first week of term 2, 27 April 2009. Research assistants will collect absence information from each school weekly. Parents of randomly selected children who have consented to participate in the post-absence interviews will be telephoned eight - nine days after the date of the first day of absence from school.

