## **Methods/Design**

### **Trial design**

The design of the trial will be a cluster randomised controlled trial (C-RCT). While this design is less efficient compared to an individually RCT, and will therefore require more children, it has been chosen for several reasons. This design will reduce contamination which would be likely to occur if students within the same school were allocated to both the hand sanitiser and standard hand washing interventions. Second, this design evaluates the effectiveness of how the intervention would be implemented in practice; with hand sanitisers installed in schools. The effectiveness of the intervention may vary if only some children within schools used the hand sanitiser compared to all children, because of the communicable nature of infectious diseases ('herd-effect'). Finally, it is more feasible to run the trial as a cluster trial since it involves less work for the teachers. As a C-RCT, teachers do not have to monitor which children use the hand sanitisers, as they would in an individually RCT.

A random selection of 50 children per school will be selected for whom detailed information about their illness absences will be sought from their parents. These children are referred hereafter as the 'follow-up children'. In addition to the 'follow-up children', absence information will be collected on all children, from the school rolls (Figure 1).

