**Table 1 Outcome measures**

| Outcome                                                                                               | Collected by                            | Timing of collection                                              | Source              |
|-------------------------------------------------------------------------------------------------------|-----------------------------------------|-------------------------------------------------------------------|---------------------|
| Primary outcome                                                                                |                                         |                                                                   |                     |
| Number of absence episodes due to any illness                                           | Telephone interview                     | 8 - 9 days after the date of the first day of absence from school | Parents of children |
| Secondary outcomes                                                                             |                                         |                                                                   |                     |
| 'Follow-up children'                                                                           |                                         |                                                                   |                     |
| Number of absence episodes due to respiratory illness                                                 | Telephone interview                     | 8 - 9 days after the date of the first day of absence from school | Parents of children |
| Number of absence episodes due to gastrointestinal illness                                            | Telephone interview                     | 8 - 9 days after the date of the first day of absence from school | Parents of children |
| Length of illness episode                                                                             | Telephone interview                     | 8 - 9 days after the date of the first day of absence from school | Parents of children |
| Length of absence episode                                                                             | Telephone interview                     | 8 - 9 days after the date of the first day of absence from school | Parents of children |

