### Secondary outcome measures

Secondary outcome measures collected on the 'follow-up children' will include the number of absence episodes due to respiratory illness, number of absence episodes due to gastrointestinal illness, length of illness episode, length of absence episode, and number of household members who become ill within one week of the participating child's illness onset (Table 1). An illness will be defined as respiratory or gastrointestinal using the definitions applied in a previous trial [13]. A respiratory illness will be defined as an acute illness that includes at least one of the following symptoms: runny nose, stuffy or blocked nose, cough, fever or chills, sore throat, or sneezing. A gastrointestinal illness will be defined as an acute illness that includes at least two watery or much looser than normal bowel movements and stools over a 24 hour period and/or vomiting. The definition of a new episode of absence due to either respiratory or gastrointestinal illness will be defined in the same way as for the primary outcome measure. The length of an absence episode will be defined as the number of days a child was absent from school for a particular episode. The length of the illness episode will be defined as the number of days between the first and last day of absence. For children who are absent on only a Monday

or only a Friday, we will define the length of the episode as two days.

Secondary outcome measures collected on all children from the school roll include the number of absence episodes and the length of an absence episode.

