#### **Economic evaluation**

One of the more challenging aspects of this study is determining the economic cost associated with children's illness and subsequent absence from school. Broadly speaking there are two basic approaches we can take to measuring these costs and we will employ both. By capturing individuals' employment circumstances and the amount of time all family members' work time is missed as a result of the illness, we can take a Human Capital approach to estimating the economic impact of the children's illness. While the Human Capital approach is widely used in economic evaluation, its use is particularly limited here as families in which no work time is lost have no cost associated with that illness. As such, we also adopt a WTP approach, asking parents to assign a value to the cost of the illness. Following the techniques described by Liu et al [28], this is done by asking parents to arrive at a figure that they would be prepared to pay to purchase a hypothetical medication that would keep their child from acquiring the same illness (i.e. same symptoms, severity and duration). The main advantage of this approach is that it allows respondents to place whatever values they deem appropriate in terms of inconvenience, lost work time and the pain and suffering of their children.

There is no clear indication in the literature in terms of the best approach to be used to arrive at a WTP figure. To avoid the risk of systematically under or over estimating WTP, each interviewer is randomly assigned an approach for each new respondent. The first approach simply asks the respondent to arrive at a figure on their own. The second approach starts with very low values and works upwards in pre-determined increments. The third approach starts with a very high value and works downwards in pre-determined increments. The questioning sequence used is available in Additional file 4 - Willingness-to-pay questioning sequence.

The analysis will provide a direct comparison between the Human Capital and the WTP approaches. We will also decompose the costs across various sub-populations

(i.e. different family structures, ethnic groups, low and high socio-economic status) to determine the extent to which the economic effect of children's illness has a different impact on different types of families, of people with different levels of extended family support and across socio-economic groups (measured by income, education and employment status).

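### As Table 1 is written, both length outcomes in follow-up children come only from a call 8-9 days after the first absence, so episodes still open or later resumed are recorded too short

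*Protocol*

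**What the plan says.** Under Timing of recruitment, intervention, and follow-up, consenting parents "will be telephoned eight - nine days after the date of the first day of absence from school". Table 1 repeats this for follow-up children. For both length of illness episode and length of absence episode, the method is telephone interview, the source is the parents, and the timing is "8 - 9 days after the date of the first day of absence from school".

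Secondary outcome measures defines the two quantities: "The length of an absence episode will be defined as the number of days a child was absent from school for a particular episode", and "The length of the illness episode will be defined as the number of days between the first and last day of absence". Under Primary outcome measure, a new episode starts only after three days free of illness absence, so a shorter return to school does not end an episode.

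The protocol also has a second stream of absence dates. Trial design says that "absence information will be collected on all children, from the school rolls", and the timing section says "Research assistants will collect absence information from each school weekly". Table 1 uses this stream for length of absence in all children, and the text agrees: "Secondary outcome measures collected on all children from the school roll include the number of absence episodes and the length of an absence episode". Nothing says that roll dates will complete the lengths in follow-up children. No second call and no rule for an episode still open at the call is described.

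**The concern.** The call is timed from the first day of absence. That suits the one-week window for illness in household members. It does not suit quantities that depend on the last day of absence, because a call cannot record a last day that has not yet happened.

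Two kinds of episode are affected:

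- the child is still absent when the parent is telephoned;
- the child has returned by the call but is absent again before three clear days have passed, so the later days belong to the same episode.

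The outcomes at stake are secondary objective (iii), average length of illness episode, and the follow-up-children version of objective (v), average length of absence episode. The loss falls on the longest episodes. Table 1 also gives length of absence two sources, of which only the interview stops at the call, so the same outcome name can carry different values for the same child.

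**Working it through.** The protocol states no figure for episode length or for the share of episodes that outlast the call, so there is no planned figure to reproduce.

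**Step 1: school days before the call.** Inputs are the call on calendar day 8 or 9 after the first absence day and a Monday-to-Friday school week. Complete school days from the first absence day up to, but not including, the call day:

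| First absence | Call on day 8 | Call on day 9 |
|---|---|---|
| Mon, Tue, Wed, Thu | 6 | 7 |
| Fri | 6 | 6 |

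If the parent also reports the call day, the limit rises by at most one. For a Monday start with a day-9 call on the Wednesday of the following week, that makes 8.

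**Step 2: closing an episode.** Three clear days must also fit before the call if the episode is to be known as finished. Counting clear days as calendar days, an unbroken absence can be confirmed as ended only if it lasted at most 3 to 5 school days. Counting them as school days, the limit is 3 or 4. The protocol's own Friday-Tuesday example fits the calendar count.

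Example: a child is absent Monday to Friday and the next Monday, present Tuesday and Wednesday, and absent Thursday. The gap is two days, so this is one episode with 7 days absent. A call on day 8 (Tuesday) or day 9 (Wednesday) records 6 days, with a last absence day of Monday instead of Thursday.

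**Step 3: illustrative size.** Assume unbroken absences with geometric length of mean μ school days, each cut at K = 6 or 7. Then:

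- share of episodes beyond the cap = (1 − 1/μ)^K
- recorded mean = μ × [1 − (1 − 1/μ)^K], so the mean is understated by that same proportion
- apparent ratio of means when the true ratio is 0.80 = 0.80 × [1 − (1 − 1/(0.8μ))^K] / [1 − (1 − 1/μ)^K], with μ the control mean

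For μ = 2 and K = 6, the share is 0.5^6 = 1.56%, the recorded mean is 1.969, and the apparent ratio is 0.80 × (1 − 0.375^6)/(1 − 0.5^6) = 0.810.

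| Assumed mean | Understatement, K = 7 to K = 6 | True ratio 0.80 appears as |
|---|---|---|
| 1.5 | 0.05% to 0.14% | not computed |
| 2 | 0.78% to 1.56% | 0.806 to 0.810 |
| 2.5 | 2.8% to 4.7% | 0.817 to 0.826 |
| 3 | 5.9% to 8.8% | 0.830 to 0.842 |

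An assumed mean of 4 would give 13% to 18%, which shows how strongly the answer depends on an unknown mean. Resumed episodes, as in Step 2, are not in this model.

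**The case against.** The best reply is that the absence dates are not lost. The roll is read weekly for all children, and length of illness is itself defined by absence dates, so the roll could supply its last day too. How to combine the sources is a derivation detail that an analysis plan may settle. Part of this stands. Objective (v) is already answered from the roll, without a cut at the call, in the larger all-children set. But Table 1 is not silent on follow-up children. It fixes the interview as the source, and following it as written gives short values. Length of illness has no roll-based row at all.

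For resumed absences, one could add that a fresh absence may trigger a fresh call. The protocol does not say whether it does, or how two calls within one episode would be joined.

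A reader might infer more than the document supports:

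- **That every long episode is lost.** It is not, because the roll holds the dates.
- **That any episode of 8 school days must be under-recorded.** This fails if the call day counts, as in Step 1.
- **That the work-loss cost-effectiveness ratio is truncated by design.** Economic evaluation says the trial will capture "the amount of time all family members' work time is missed as a result of the illness" but gives no call or date, and Table 1 has no row for it. This call is the likely occasion, since the only other parent interview described comes after the intervention period and concerns skin reactions. That remains an inference.
- **That a real difference between arms would be hidden.** The call timing is the same in both arms, and the illustration shows only slight attenuation.

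**Conclusion.** The point holds as a fault in the stated source and timing of two secondary outcomes in follow-up children. A call preceded by 6 or 7 complete school days cannot give the length of an episode that is unfinished or later resumed, and the protocol states no means of completing it. The primary outcome is a count of episodes and is outside this point.

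The size is unknown. Under geometric lengths with an assumed mean of 1.5 to 3 school days, the mean is understated by about 0.05% to 9%, and by 0.8% to 1.6% at a mean of 2. If most absences last a day or two, the bias is small. The case for correcting it is that the stated source does not match the stated definitions and better dates are already being collected.

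**What to change.** In Table 1 and under Secondary outcome measures, state that for follow-up children:

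- length of absence episode and length of illness episode are derived from the weekly school-roll absence dates, with the three-day rule applied to those dates;
- the interview supplies the reason for absence, symptoms and household illness, and stays at 8-9 days;
- a stated rule covers the reason for days absent after the call, which will have no parent report.

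Confirm the linkage before relying on it. Ethical review calls the roll data anonymised, and the written consent described there is for post-absence interviews. Linkage looks workable, because the research assistants record the selected children's names and classes and individual absences must be seen to trigger each call. Consent and wording should still be shown to cover it for the consented children.

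Under Economic evaluation, state when parents' lost work time is recorded, and how this is handled for an episode open at the call. The roll cannot supply that item. A short completion call is one option, but the core change does not depend on it.

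The cost is a wording change and a linkage check, with no new collection of absence dates. If the present consent does not cover linkage, amending it is a further cost.

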#### **Trial outcomes**

##### **Primary outcome measure**

The primary outcome measure for this trial is the number of absence episodes due to *any* illness over 20 weeks; excluding injuries and infestation (head lice and scabies) (Table 1). Absence due to *any* illness has been selected as our primary outcome, in preference to absences due to infectious illness because of difficulties in accurately diagnosing the illness through interviews with the children's parents. The definition of a new episode of absence due to illness has been variously defined between trials. For example, Guinan et al [11] defined a new episode of absence due to illness as one in which there was a lapse of at least five days between a previous period of absence due to illness. Other trials have defined a new episode of absence due to illness as one where the child is absent for at least one day in a given week [10]. We will define a new episode of absence due to illness as one in which there have been at least three days with no absences due to illness. So, for example, if a child is absent from school on Friday, present on Monday, and absent on Tuesday; this will constitute two absences. However, if a child is absent from school on a Tuesday, present on Wednesday, and absent again on Thursday; this will constitute one absence. While there is no theoretical justification for any particular definition for a new episode of absence due to illness, an absence period of at least three days has the advantage of classifying a child who is absent on a Friday and Monday as having only one absence episode, and further, this definition has been used previously [21].

**Table 1 Outcome measures**

| Outcome                                                                                               | Collected by                            | Timing of collection                                              | Source              |
|-------------------------------------------------------------------------------------------------------|-----------------------------------------|-------------------------------------------------------------------|---------------------|
| Primary outcome                                                                                |                                         |                                                                   |                     |
| Number of absence episodes due to any illness                                           | Telephone interview                     | 8 - 9 days after the date of the first day of absence from school | Parents of children |
| Secondary outcomes                                                                             |                                         |                                                                   |                     |
| 'Follow-up children'                                                                           |                                         |                                                                   |                     |
| Number of absence episodes due to respiratory illness                                                 | Telephone interview                     | 8 - 9 days after the date of the first day of absence from school | Parents of children |
| Number of absence episodes due to gastrointestinal illness                                            | Telephone interview                     | 8 - 9 days after the date of the first day of absence from school | Parents of children |
| Length of illness episode                                                                             | Telephone interview                     | 8 - 9 days after the date of the first day of absence from school | Parents of children |
| Length of absence episode                                                                             | Telephone interview                     | 8 - 9 days after the date of the first day of absence from school | Parents of children |
| Number of household members who become ill within one week of the participating child's illness onset | Telephone interview                     | 8 - 9 days after the date of the first day of absence from school | Parents of children |
| All children                                                                                   |                                         |                                                                   |                     |
| Number of absence episodes for any reason                                                             | Liaison research assistant  | Weekly                                                            | School roll         |
| Length of absence episode                                                                             | Liaison research assistant  | Weekly                                                            | School roll         |
| Adverse events                                                                                 |                                         |                                                                   |                     |
| Skin reactions                                                                            | Telephone interview                     | Following the intervention period                                 | Parents of children |

 'Follow-up children' only.

 Parents will not be telephoned where it is clear that the child was not unwell (for example, on a holiday, attended a funeral, etc).

 Through contact with school staff or by extracting the data in person.

